## Abstract

**Introduction:** Patients with type 2 diabetes mellitus are at high risk to develop vascular complications resulting in high morbidity and mortality. Cocoa flavanols are promising nutraceuticals with possible beneficial vascular effects in humans. However, limited research is currently available on the vascular effects in a diabetic population with inconsistent results. Possible reasons for this inconsistency might be heterogeneity in the given intervention (dose per time and day, single dose vs. split-dose, placebo formula) and the studied population (blood pressure at baseline, duration of diabetes, use of vasoactive antihypertensive and antidiabetic drugs, sex). Therefore, we aimed to develop a randomized, double-blinded, placebo-controlled cross-over trial to investigate whether cocoa flavanols have an acute impact on blood pressure and vascular reactivity in patients with type 2 diabetes with and without arterial hypertension.

**Methods and Analysis:** We will include participants in four groups: (i) patients with type 2 diabetes without arterial hypertension, (ii) patients with type 2 diabetes with arterial hypertension and 1 antihypertensive drug, (iii) non-diabetic participants with essential hypertension and 1 antihypertensive drug, and (iv) healthy controls. All participants will complete the same protocol on both testing days, consuming high-flavanol cocoa extract (790 mg flavanols) or placebo. Macrovascular endothelial function (flow-mediated dilation) and blood pressure will be measured before and after capsule ingestion. Forearm muscle vasoreactivity (near-infrared spectroscopy) and brachial artery blood flow (echo-doppler) will be assessed in response to a dynamic handgrip exercise test after capsule ingestion. Data will be analyzed with a random intercept model in mixed models.

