This acute, randomized, double-blinded, placebo-controlled cross-over study aims to investigate whether a single intake of a high dose of CF (790 mg flavanols) induces an improvement in endothelial function (primary outcome), a reduction in BP, and an enhancement in muscle vasoreactivity and oxygenation in patients with T2DM compared to healthy controls.

Because hypertension is a common comorbidity in patients with T2DM and as little is known so far concerning possible interferences between antihypertensive drugs and CF actions especially in patients with diabetes mellitus, this study will additionally investigate possible influence of beta-blockers (BB), angiotensin converting enzyme inhibitor (ACEi), or angiotensin receptor blocker (ARB) in diabetic persons with arterial hypertension and non-diabetic persons with essential hypertension treated with these drugs.

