### Intervention

#### Study Protocol

As depicted in Figure 1, patients will arrive at the lab (Ghent University Hospital) at 8 o'clock after an overnight fast of minimal 8 h. Blood samples will be collected and participants will be evaluated for body composition [weight, height, skinfolds, and fat% (bio-electrical impedance analyzer)] and BP, followed by a standardized breakfast with negligible flavonoid and nitrate/nitrite amounts, in accordance to guidelines of a dietician (Table 3), and consumed within 15 min. Participants have to choose 1 formula of breakfast which will be consumed at both visits. After 15 min rest period, a baseline Flow-Mediated Dilation (FMD) measurement will be performed, followed by the ingestion of CF-enriched capsules (2.5 g of cocoa extract which contains 790 mg flavanols of which 150 mg epicatechin, *Naturex*^©^, *France*) or placebo (maltodextrin and an equivalent dose of theobromine and caffeine compared to the CF-enriched capsules) (Table 4). The dose of CF given in this study is based on the research of Balzer et al. (41) who investigated the effect of different doses of CF (high dose = 963 mg CF of which 203 mg epicatechin, medium dose = 371 mg CF of which 78.9 mg epicatechin, and low dose (control) = 75 mg CF of which 16.8 mg epicatechin), closely matched for theobromine and caffeine, on FMD in 10 patients with T2DM. The equilibration of theobromine and caffeine, both vasoactive compounds of cocoa (38, 56, 57), in the different interventions is a very important quality of this study and will ensure to test isolated vascular effects of CF.

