#### Data-Analysis Plan

Effects of CF ingestion on primary and secondary outcome measures will be evaluated within and between groups. Data will be analyzed using a random intercept model in mixed models. Fixed effects will be the group, the supplementation (cocoa flavanols vs. placebo), the time (pre- vs. post-intake of capsules) during each visit for repeated measurements, as well as group × supplementation interaction and time × supplementation interactions. We will also consider the order of both visits in a first intent and this factor will be kept in analyses only if significant. As all groups are matched by age, sex, and BMI, only medication intake, level of physical activity, glycemic excursions, risk for hypo- or hyperglycemia, and glycemic variability will be considered as covariates when analyzing data. In case of drop-outs or missing data, the participant is still included in data analysis providing one out of two visits is completed.

Results will be presented as mean ± standard deviation with its corresponding 95% confidence interval. Level of significance will be set at *p* < 0.05. Data analysis will be conducted using IBM SPSS statistics version 26.

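### For FMD and blood pressure, the listed mixed model has no group × time × supplementation term, so its between-group estimate is half the true difference in cocoa-flavanol effect

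*Protocol article*

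**What the plan says.** The Data-Analysis Plan of the protocol article sets the goal: "Effects of CF ingestion on primary and secondary outcome measures will be evaluated within and between groups". It then fixes the method: "Data will be analyzed using a random intercept model in mixed models". The fixed effects are group, supplementation and "the time (pre- vs. post-intake of capsules) during each visit for repeated measurements", "as well as group × supplementation interaction and time × supplementation interactions". Neither group × time nor group × time × supplementation is named.

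The outcomes do not all have the same structure. The Abstract states: "Macrovascular endothelial function (flow-mediated dilation) and blood pressure will be measured before and after capsule ingestion". The Study Protocol section confirms the order for the primary outcome: "a baseline Flow-Mediated Dilation (FMD) measurement will be performed, followed by the ingestion of CF-enriched capsules". The handgrip outcomes (muscle oxygenation by NIRS, and brachial blood flow) differ. According to the Abstract, they "will be assessed in response to a dynamic handgrip exercise test after capsule ingestion".

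The aim at the end of the Introduction is a comparison of T2DM with healthy controls. It covers endothelial function and blood pressure, and its last clause reads "an enhancement in muscle vasoreactivity and oxygenation in patients with T2DM compared to healthy controls". The Introduction also hopes to find out whether medication makes some patients non-responders.

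**The concern.** For an outcome measured before and after intake, the cocoa-flavanol effect in a group is the CF-minus-placebo difference in change. Whether that effect differs between groups is a three-way question: group × time × supplementation. Neither listed interaction expresses it. Group × supplementation compares groups on a CF-minus-placebo difference averaged over both time points, and half of those data precede any capsule. Time × supplementation isolates the change, but as one value shared by all four groups.

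The size of the response in T2DM relative to controls, and the recognition of a group that does not respond, are therefore at stake for the primary outcome and for blood pressure. The only baseline-adjusted effect in a four-group fit is a pooled one, and 50 of the 75 planned participants (30 + 20, or 67%) do not have diabetes.

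**Working it through.** **Inputs.** Group sizes come from Eligibility Criteria: T2DM with hypertension 15, T2DM without hypertension 10, essential hypertension 30, healthy 20 (total 75). The fixed effects come from the Data-Analysis Plan. Because the baseline measurement precedes the capsules, the expected CF-minus-placebo difference before intake is 0 in every group. The documents give no group-specific effects and no FMD standard deviation, so the effect sizes below are assumptions. No figure in the plan depends on this point, so there is none to reproduce.

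**Step 1: what the listed model can fit.** Let d_g be the true post-intake effect in group g. The CF-minus-placebo difference in group g is then 0 before intake and d_g after. In the listed model this difference has the form a + b_g + c·t, with t = 0 before and t = 1 after. Here b_g is group × supplementation and c is time × supplementation. With complete data, least squares gives:

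- c = d̄, the size-weighted mean of the d_g. Every group is given this same change-from-baseline effect.
- a + b_g + c/2 = d_g/2 (the fitted group average equals the observed one), so b_g − b_h = (d_g − d_h)/2.
- Fitted post-intake effect = (d_g + d̄)/2.
- Fitted pre-intake effect = (d_g − d̄)/2, where the truth is 0.

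The factor of one half does not depend on group sizes or effect sizes.

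**Step 2: numbers.** Suppose the effect is 2 FMD points in both T2DM groups and 0 elsewhere. Then d̄ = (15 × 2 + 10 × 2)/75 = 0.667, and:

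- T2DM minus healthy: (2 − 0)/2 = 1.0 (truth 2.0).
- Fitted post-intake effect: (2 + 0.667)/2 = 1.33 in T2DM (truth 2.0), and (0 + 0.667)/2 = 0.33 in the other groups (truth 0).
- Fitted pre-intake effect: (2 − 0.667)/2 = +0.67 in T2DM, and −0.33 in the other groups (truth 0).

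Other assumed patterns, in the order T2DM with hypertension / T2DM / hypertension / healthy:

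| True post-intake effects | d̄ | Fitted post-intake effects | T2DM with hypertension minus healthy: fitted (true) |
|---|---|---|---|
| 0 / 2 / 0 / 2 | 0.8 | 0.4 / 1.4 / 0.4 / 1.4 | −1.0 (−2.0) |
| 0.5 / 1 / 1 / 2 | 1.167 | 0.833 / 1.083 / 1.083 / 1.583 | −0.75 (−1.5) |
| 0 / 0 / 0 / 2 | 0.533 | 0.267 / 0.267 / 0.267 / 1.267 | −1.0 (−2.0) |

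If all d_g are equal, then d_g = d̄. The fitted post-intake effects are correct, and the between-group difference is correctly 0.

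**Step 3: with the missing terms.** Adding group × time and group × time × supplementation recovers the true between-group differences exactly in noise-free data.

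**Step 4: the test rather than the estimate.** Let s² be the residual variance in a random-intercept model. The per-person averaged contrast has variance s²/2 + s²/2 = s². The change contrast (two post values and two pre values) has variance 4s². The ratios 1.0/s and 2.0/(2s) are the same. A simulation of the 0 / 2 / 0 / 2 pattern agreed. It used 200 trials per setting, with assumed SDs of 2 between persons, 1.5 residual and 0 or 1 between visits:

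| Visit SD | Mean estimate, listed model | Mean estimate, three-way model | Power, listed | Power, three-way |
|---|---|---|---|---|
| 0 | −0.985 | −2.091 | 0.47 | 0.515 |
| 1 | −1.018 | −2.05 | 0.385 | 0.42 |

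The true difference is −2.0. The estimate is halved, while power is only slightly lower.

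**The case against.** Four points can be made for the plan.

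1. **The between-group test survives.** A reader might infer that the trial loses its between-group test or half its power. The documents do not support that. If all groups respond equally, the expected group × supplementation coefficient is zero, and the halved coefficient comes with a standard error that is about halved. This stands and limits the point to estimation.

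2. **Some outcomes are unaffected.** A reader might take the whole model to be wrong. For NIRS and blood flow, which are measured only after intake, the time factor drops out and group × supplementation is the right contrast. This stands. The muscle-oxygenation clause of the aim therefore shows which groups are compared; it does not name an outcome that is harmed.

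3. **Within-group effects might come from separate fits.** The plan promises evaluation within groups but does not say that those effects are contrasts from one four-group fit. If each group were analysed alone, time × supplementation would be that group's own effect, and nothing would be pulled towards a pooled mean. This stands as a condition. The within-group distortion holds only for a single pooled fit, which is what a model with group as a fixed effect suggests but does not settle. The halving of the between-group estimate is unaffected.

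4. **The article is condensed.** A separate analysis plan might add the terms, and the plural used for the time × supplementation interactions is loose. But the article lists its fixed effects explicitly, and no three-way term is among them. The point concerns what is stated, not a detail left out.

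**Conclusion.** For FMD and blood pressure the model is wrong as written for the stated aim. With complete pre- and post-intake data and no effect before the capsules, its between-group term is exactly half the true difference. In one pooled four-group fit, each group's post-intake effect also lies halfway between its own value and the pooled mean, and the change-from-baseline effect is identical in all groups. The values 1.0, 1.33 and 0.33 rest on the assumed pattern of 2 points in T2DM and 0 elsewhere. Only the factors are general.

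The consequence is understated group differences, confidence intervals on the wrong scale, and groups that do not respond being credited with part of the others' response. Under the random-intercept model's own assumptions, the validity of the between-group test is not in question.

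**What to change.** For FMD and blood pressure, add group × time and group × time × supplementation to the fixed effects. Name the T2DM-versus-healthy contrast of the three-way term as the between-group estimate, and say whether it is taken for each T2DM group or for both combined. Take each group's cocoa-flavanol effect from its own time × supplementation contrast, and report it with a 95% confidence interval.

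An alternative is to model the post-intake value on group × supplementation, with the same visit's pre-intake value as covariate. It has the same target but is a different estimator and can give different numbers, so one of the two should be chosen in advance.

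Keep group × supplementation without time for the handgrip NIRS and blood-flow outcomes.

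The cost is one line in the analysis plan and six further fixed-effect parameters (3 + 3 with four groups). No new data are needed. The between-group confidence interval will be about twice as wide as that of the halved coefficient, because it then refers to the full difference.

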### Participants

#### Eligibility Criteria

All subjects are divided in four groups: (i) patients with T2DM with arterial hypertension (with BB, *n* = 5/ACEi, *n* = 5/ARB, *n* = 5) (*n* = 15), (ii) patients with T2DM without arterial hypertension (*n* = 10), (iii) non-diabetic patients with essential arterial hypertension (BB, *n* = 10/ACEi, *n* = 10/ARB, *n* = 10) (*n* = 30), and (iv) healthy participants (control group; *n* = 20).

Inclusion and exclusion criteria are summarized in Table 2.

**Table 2 T2:** In- and exclusion criteria for participants in this study.

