#### Blinding and Randomization

In this cross-over study, every participant will receive CF-enriched and placebo capsules. Randomization of capsules will be done by sealed envelopes and type of capsules will be indicated by number 1 or number 2. Each participant may choose 1 envelope at the first study day. Both types of capsules have an identical look and taste. Hence, participants will be blinded to their group allocation. Furthermore, since type of capsules will be identified by numbers, outcome assessors and personnel involved in data collection and data analysis will be blinded to participants' group allocation throughout the entire trial.

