### Statistical Analyses

#### Power and Sample Size Calculation

Sample size calculations are based on previous research focusing on interventional studies with FMD measurements (77, 78) who established that in cross-over trials at least 20–30 participants are required for a minimal detectable change of 1.5–2% in FMD (80% power, alpha-level = 0.05). Sample size calculation was done by SAS power and sample size, indicating a minimum of nine participants in each group (41). Data will be analyzed taking into account volunteer- and methodology-related factors (79).

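### Visit order is kept only if significant, so a real visit shift can stay in the group × supplementation contrast and in the outcomes measured only after intake

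*Protocol article*

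**What the plan says.** The Data-Analysis Plan describes a mixed model with a participant-level random intercept. Its fixed effects are group, supplementation and time (before or after intake), plus group × supplementation and time × supplementation. There is no three-way term. On visit order it says: "We will also consider the order of both visits in a first intent and this factor will be kept in analyses only if significant". It also says: "Level of significance will be set at *p* < 0.05". A participant who completes only one of the two visits stays in the analysis.

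Under Blinding and Randomization: "Randomization of capsules will be done by sealed envelopes and type of capsules will be indicated by number 1 or number 2". The next sentence reads: "Each participant may choose 1 envelope at the first study day". Neither blocking nor stratification by group is mentioned, either way.

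Eligibility Criteria gives groups of 10 (T2DM without hypertension), 15 (T2DM with hypertension), 30 (essential hypertension) and 20 (healthy), 75 in all. FMD and BP are measured before and after intake at each visit. Handgrip NIRS and brachial blood flow are measured only after intake.

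**The concern.** In a two-period cross-over each participant contributes one CF-minus-placebo difference. A general change from visit 1 to visit 2 raises that difference in participants who take CF second and lowers it in those who take CF first. If the two sequences are equally frequent in a group, the shifts cancel. If they are not, a model without a visit term attributes part of the shift to CF. Keeping the term only after a significant test makes the model depend on the data, and the later p-values and intervals ignore that step. A non-significant result in a small sample is weak evidence that there is no shift.

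At stake is the comparison of CF response between groups. Because the model has no group × time × supplementation term, that comparison rests on group × supplementation, which is not corrected for the pre-intake value. The post-only handgrip outcomes have no pre-intake value at all, and a maximal test to exhaustion is one where familiarisation is plausible. Keeping participants with a single visit can add to the imbalance.

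**Working it through.** **Inputs.** Group sizes and the model terms come from the article. The article gives no figure for a visit shift and no SD, so both are assumed: shift π of 0.5 to 2 FMD points, SD of within-person differences of 2 to 3 FMD points. Tests are taken as two-sided at 0.05.

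**The plan's own figures, and where the SD range lies.** Power and Sample Size Calculation cites that "in cross-over trials at least 20–30 participants are required for a minimal detectable change of 1.5–2% in FMD (80% power, alpha-level = 0.05"), and gives a minimum of nine per group. Without an SD neither figure can be reproduced, but each implies one.
- From SD = δ√n / (1.96 + 0.84): 2 × √20 / 2.80 = 3.19 and 1.5 × √30 / 2.80 = 2.93. The exact paired t version gives 3.03 and 2.83.
- Nine participants at 80% power imply a standardised effect of 1.07, so an SD of 1.5/1.07 = 1.41 (rounding as computed) or 2/1.07 = 1.87.

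The assumed 2–3 lies between these two sets.

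**Bias when the term is dropped.** Let τ be the true CF effect and let k of n participants take CF at visit 2. The expected difference is τ + π for those k and τ − π for the rest. The group mean is τ + π(2k − n)/n.
- n = 10, split 7:3: (7 − 3)/10 = 0.40π
- n = 10, split 8:2: (8 − 2)/10 = 0.60π
- n = 15, split 10:5: (10 − 5)/15 = 0.33π
- n = 10, split 5:5: 0

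With π = 1 point and a 7:3 split, 0.40 points remain. Against the cited target this is 0.40/2 = 20% to 0.40/1.5 = 27%.

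**Chance of such a split at n = 10.** With simple 50:50 allocation, 2 × P(X ≤ 3) = 2 × 176/1024 = 0.344. If the envelope pool is balanced 38:37 overall but not by group, the hypergeometric probability is 0.309. Only balance within each group removes the risk.

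**Which terms are exposed.** I fitted the stated fixed effects (participant terms standing in for the random intercept) to noise-free data with zero CF effect, a 1-point visit shift, a 7:3 split in the n = 10 group, 10:5 in the n = 15 group, and even splits elsewhere.

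| Term | No visit term | With visit term |
|---|---|---|
| group × supplementation, n = 10 | 0.40 | 0.00 |
| group × supplementation, n = 15 | 0.33 | 0.00 |
| time × supplementation | 0.00 | 0.00 |

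The last row is zero because an additive visit shift is in both the pre and the post value of a visit and subtracts out.

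**Chance that the rule keeps a real shift (simulation; SD 3 to SD 2).**

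| Test run on | π = 0.5 | π = 1 |
|---|---|---|
| n = 10 | 7.5–10% | 14–26% |
| n = 15 | not needed | 21–41% |
| all 75 | 30–56% | 81–99% |

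**Type I error at n = 10, test run within the group.** Averaged over 50:50 allocation it is about 6–7%. Given a realised 7:3 split it is 6.7–7.6%, and given 8:2 it is 8.9–13.5%, for shifts of 1 to 2 points. With visit always fitted it is about 5% throughout.

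**The case against.** The strongest reply is that the plan describes one model over all groups, so the natural reading is a single order test on 75 participants. A 1-point shift would then be dropped only 1–19% of the time. Harm also needs an uneven split: treating the two as independent, (0.01 to 0.19) × 0.34 is about 0.3–6.5% for the n = 10 group. This stands and limits the size of the problem. It is weaker for a 0.5-point shift, dropped 44–70% of the time, although that leaves only 0.40 × 0.5 = 0.2 points at 7:3.

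The article also describes steps that limit drift in FMD: at least 100 supervised scans before the start, one blinded reader, the same breakfast at both visits and the same meal the evening before. And the bias averages to zero over the randomisation; the harm is conditional on the split that occurs. Both points stand.

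A reader might infer more than the article supports:
- **That the envelopes were unblocked.** The article is silent, and a condensed article may leave this to the full protocol.
- **That every CF estimate is biased, including the pre/post FMD contrast.** An additive visit shift cancels there.
- **That drug-class cells of five are the worst case.** A 4:1 or worse split does have a 38% chance per cell (2 × 6/32), and 76% in at least one of three (1 − 0.625³). But the plan treats medication as a covariate and specifies no CF contrast per cell.
- **That carry-over is pre-tested.** No such test is described.

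None of this justifies choosing a design factor by its p-value.

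**Conclusion.** The point holds in a limited form. The retention rule is explicit and is a poor one for a two-period cross-over. It leaves group × supplementation and the post-intake-only NIRS and blood-flow outcomes open to a visit shift whenever the term is dropped and sequences are uneven within a group. The size is modest. The most clearly exposed group is the n = 10 group, and the larger error rates need an 8:2 split, which has about an 11% chance (8:2 or worse) under simple allocation. If the test is pooled over all participants, it is mainly shifts well below 1 point that would be missed.

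These sizes rest on the assumed shift and SD in FMD points. The article gives no figures from which to size the shift for the handgrip outcomes. The case for the change rests on its low cost and on the rule having no compensating benefit, not on a demonstrated large bias.

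**What to change.** Include visit number (1 or 2) as a fixed effect in every model, whatever its p-value, and delete the rule that keeps it only if significant. Say that order means visit number: a main effect of treatment sequence would not remove a visit shift. The fix works however the envelopes were made up.

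The cost is about one degree of freedom. Study Setting and Organization puts the end of the study in June 2021, after the article's publication in March 2021, so the model could be settled before unblinding.

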**Inclusion criteria**
Male and female; age: 18–85 years; BMI: 20–40 kg/m^2^
(i) Patients with T2DM without arterial hypertension: at least 5 years T2DM [HbA1c ≥6.5%, glucose (fasting) ≥126 mg/dl, glucose (not fasting): ≥200 mg/dl, defined by the American Diabetes Association (ADA) (55)]
(ii) Patients with T2DM with arterial hypertension: at least 5 years T2DM [HbA1c ≥6.5%, glucose (fasting) ≥126 mg/dl, glucose (not fasting): ≥200 mg/dl, defined by the American Diabetes Association (ADA) (55)] AND at least 1 year arterial hypertension taking BB, ACEi or ARB (optionally combined with diuretics)
(iii) Patients with essential arterial hypertension: at least 1 year arterial hypertension taking BB, ACEi or ARB (optionally combined with diuretics), matched by age, sex, and BMI with subjects with T2DM
(iv) Healthy controls: taking no medication except for contraceptive drugs, matched by age, sex, and BMI with subjects with T2DM

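### Age, sex and BMI are left out on a matching claim wider than Table 2 supports, while covariates that largely encode group are kept in a model that contains group

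*Protocol article*

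**What the plan says.** The Data-Analysis Plan of the protocol article evaluates the effects of cocoa flavanols within and between groups. It uses a random intercept model with group, supplementation, time, group × supplementation and time × supplementation. On covariates it says: "As all groups are matched by age, sex, and BMI, only medication intake, level of physical activity, glycemic excursions", then "risk for hypo- or hyperglycemia, and glycemic variability will be considered as covariates when analyzing data". The word *only* closes the list, and matching is the sole reason given.

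Table 2 states the matching. Healthy participants enter as "Healthy controls: taking no medication except for contraceptive drugs, matched by age, sex, and BMI with subjects with T2DM", and the essential-hypertension group carries the same condition: "matched by age, sex, and BMI with subjects with T2DM". Neither T2DM group has a matching condition. The general limits are "Male and female; age: 18–85 years; BMI: 20–40 kg/m^2".

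Table 2 also defines the groups by what the analysis then adjusts for. Both T2DM groups need "at least 5 years T2DM [HbA1c ≥6.5%, glucose (fasting) ≥126 mg/dl" and further glucose limits. Both hypertensive groups need "at least 1 year arterial hypertension taking BB, ACEi or ARB (optionally combined with diuretics".

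Eligibility Criteria plans 15 participants with T2DM and hypertension (5 per drug class), 10 with T2DM alone, 30 with essential hypertension (10 per drug class) and 20 healthy controls. Additional Outcome Measures places the glucose monitoring and accelerometry in the week directly after the second study day.

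**The concern.** Supplement order is randomised within each person, but group is not randomised. A difference between groups, in level or in response to cocoa flavanols, can therefore reflect age, sex or BMI as well as diabetes or hypertension. The plan sets these three aside on a premise that its own inclusion table supports only in part. The gap lies at T2DM with versus without hypertension, a comparison the study needs because the Introduction asks how antihypertensive drugs bear on the response in diabetes.

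The covariates that are kept raise the opposite problem. Antihypertensive treatment and glycaemia are much of what makes the groups different. Adjusting a group contrast for them either leaves it without a unique estimate or removes part of the difference it is meant to show.

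**Working it through.** **1. How far the matching reaches.** Two groups (30 and 20) are matched to the T2DM subjects, 15 + 10 = 25 in all. Take this as matching to the pooled 25, and suppose the two T2DM groups differ in mean age by D. The pooled mean then lies 10/25 = 0.4D from the T2DM + hypertension mean and 15/25 = 0.6D from the T2DM-only mean. Perfect matching on the pooled mean would still leave gaps of 0.4D, 0.6D and D in the contrasts that involve a single T2DM group. The documents give no value for D, and it may be small. The point is that Table 2 does not constrain it.

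**2. Medication against group.** Inputs: sizes 15, 10, 30, 20, total 75. Every hypertensive participant takes a beta-blocker, ACE inhibitor or ARB, and healthy controls take none (Table 2). Assumption: T2DM patients without hypertension take no antihypertensive.

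- Yes/no coding: users = 15 + 30 = 45, so the indicator equals the sum of the two hypertensive-group columns. Group (4 columns) plus indicator (1) gives 5 columns, rank 4.
- Drug-class coding: BB + ACEi + ARB equals the same sum. Group (4) plus class (3) gives 7 columns, rank 6.

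In both cases the single dependency puts weight 1 on each hypertensive group and 0 on the other two. A group contrast is estimable only if these weights cancel:

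| Contrast | Weights | Estimable |
|---|---|---|
| T2DM+HT vs HT | 1 − 1 = 0 | yes |
| T2DM vs healthy | 0 − 0 = 0 | yes |
| T2DM+HT vs T2DM | 1 − 0 = 1 | no |
| T2DM+HT vs healthy | 1 − 0 = 1 | no |
| HT vs healthy | 1 − 0 = 1 | no |
| T2DM vs HT | 0 − 1 = −1 | no |

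The four lost contrasts are all those that set a hypertensive group against a non-hypertensive one. Suppose also that every T2DM participant, and nobody else, takes an antidiabetic drug, which the documents do not state. Adding that indicator gives 8 columns, rank 6, and none of the six contrasts is estimable.

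**3. Which estimates are touched.** Let x be a covariate with one value per participant.

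- Main effect only: response on cocoa flavanols minus response on placebo = (… + βx) − (… + βx), so βx cancels. With complete visits the supplementation and group × supplementation estimates do not move. The group main effect does.
- Interacted with supplementation: the difference becomes group effect + γx. The design of step 2 now applies to the differences. Yes/no use and its interaction give 10 columns, rank 8. With drug class the same four group × supplementation contrasts are lost.

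**4. Illustration on simulated data.** This used the planned sizes with an assumed age imbalance, an assumed age effect on FMD and an assumed glycaemic index that is higher in T2DM. It shows the mechanism and does not forecast a size.

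| Covariates added | T2DM+HT vs healthy, main effect (SE) | Same group × supplementation (SE) | Time × supplementation (SE) |
|---|---|---|---|
| none | −2.105 (0.762) | 0.296 (0.511) | 0.606 (0.345) |
| age, sex, BMI | −1.347 (0.834) | 0.296 (0.511) | 0.606 (0.345) |
| glycaemic index | −1.564 (0.907) | 0.296 (0.511) | 0.606 (0.345) |

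With 8 of the 75 reduced to one visit, adding covariates moved the two interaction terms by at most 0.005.

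**5. Timing.** The glycaemic indices are recorded after both products have been taken, so they are not baseline characteristics. Accelerometry shares this timing, but physical activity defines no group.

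**The case against.** The strongest reply is that the trial's main question is a within-person one. The effect of cocoa flavanols is carried by supplementation and its interactions, and step 3 shows that participant-level main effects do not alter these in complete data. The plan states no covariate × supplementation term. This stands, and it limits the harm to between-group contrasts. It does not remove the harm, because the plan commits to evaluating effects between groups. Main effects alone do nothing to adjust the comparison of responses, and the interactions that would adjust it bring the aliasing with them.

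A reader might infer that Table 2 contradicts the matching claim, or that sizes of 15, 10, 30 and 20 rule matching out. Neither follows. Table 2 is silent on the two T2DM groups, one-to-one matching is nowhere claimed, and matching of distributions is compatible with unequal sizes. The wide age and BMI limits are eligibility bounds and do not show imbalance.

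Medication intake could also be coded in other ways. Drug class, diuretics, insulin and other antidiabetic drugs vary within groups, so full aliasing is a property of particular codings. Studying drugs is an explicit aim, and the Abstract's list of possible reasons for inconsistent results names drugs beside sex: "blood pressure at baseline, duration of diabetes, use of vasoactive antihypertensive and antidiabetic drugs, sex". That supports analysing medication. It does not make medication a suitable nuisance adjustment for a contrast it helps to define.

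Finally, the listed glycaemic covariates are continuous-monitoring indices, not the diagnostic criteria, and no document gives their distribution by group. A tie to diabetes status is a fair expectation, but near-complete separation would be an assumption. The text also says these covariates will be considered, so the damage depends on how the model is built.

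**Conclusion.** The point holds for the between-group analysis. The reason given for omitting age, sex and BMI goes further than Table 2, which leaves the two T2DM groups unmatched to each other. Medication largely encodes group: with antihypertensive use or drug class in the model, 4 of 6 group contrasts are not estimable, provided that T2DM patients without hypertension take no antihypertensive. The glycaemic indices are tied to the diabetes exposure and are measured after both interventions.

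It would be tempting to call the whole covariate list the wrong way round, or to say that the cocoa flavanol effect itself is biased. The documents support neither. Physical activity defines no group, drug class can be estimated within the hypertensive groups, and the cocoa flavanol versus placebo contrast is untouched by participant-level main effects when visits are complete. The size of any confounding by age, sex or BMI cannot be derived from the documents.

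**What to change.** - Limit the matching statement to what Table 2 supports: the essential-hypertension and healthy groups are matched to the T2DM subjects as a whole.
- Prespecify age, sex and BMI as covariates for between-group comparisons. Where groups are compared on their response to cocoa flavanols, add each covariate × supplementation, possibly as a sensitivity analysis because one group has only 10 participants.
- Keep group-defining medication and the glycaemic indices out of the main model with all four groups.
- Analyse drug class × supplementation within the two hypertensive groups, where group may stay in the model, and glycaemic indices within the T2DM groups. Label both exploratory, since classes hold 5 or 10 participants.
- Physical activity may stay.

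The cost is in analysis wording, since age, sex and BMI are already needed for eligibility and matching. Three main effects and three supplementation interactions add 6 parameters. Carrying them through time as well (3 × time, 3 three-way) makes 12. On the per-person differences, three slopes beside four group means take the residual degrees of freedom from 75 − 4 = 71 to 75 − 7 = 68. Intervals for between-group contrasts may widen slightly.
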